## Classification of Contraceptive Methods based on their Effectiveness.

**Table A3.** Classification of Contraceptive Methods based on their Effectiveness.

| Effectiveness                      | Examples                                                                                                                                                                                                                                                                                                                                                                                                                                                                                                                                                                                                                                                                                                                                                                       |
|------------------------------------|--------------------------------------------------------------------------------------------------------------------------------------------------------------------------------------------------------------------------------------------------------------------------------------------------------------------------------------------------------------------------------------------------------------------------------------------------------------------------------------------------------------------------------------------------------------------------------------------------------------------------------------------------------------------------------------------------------------------------------------------------------------------------------|
| Highly effective contraception     | ORAL 
 
- Combination oral contraceptive pills
 
- Mini pill
 
 NON-ORAL 
 
- Implanted contraceptives
 
- Injectable contraceptives
 
- Contraceptive patch (only women <90 kg)
 
- Total abstinence (if this is their preferred usual lifestyle)
 
- Vasectomy (partner)
 
- Fallopian tube implants (if confirmed by hysterosalpingogram)
 
- Combined contraceptive vaginal ring
 
- Intrauterine devices.
 
                                                                                                                                                                                             |
| Effective contraception            | 
 
- Male or female condoms with spermicide
 
- Diaphragms with spermicide or cervical sponges
 
                                                                                                                                                                                                                                                                                                                                                                                                                                                                                                                                                                                                                           |
| Ineffective forms of contraception | 
 
- Barrier protection methods without the concomitant use of a spermicide
 
- Use of male and female condoms as a double barrier method due to the high failure rate when these methods are combined. 
 
✓ Spermicide alone
 
✓ Immunocontraceptives
 
✓ Periodic abstinence
 
 
 
 Fertility awareness or post-ovulation methods 
 
✓ Calendar method.
 
✓ Temperature method.
 
✓ Combination of the above 2
 
✓ Cervical mucus.
 
✓ Symptothermal.
 
 
 
- Withdrawal
 
- Post-coital douche
 
- Lactational amenorrhea
 
 |

## Contraception Requirements for Female Participants

All females should follow the contraception guidance in Table A4 for the entirety of the study and 30 days thereafter.

**Table A4. Contraception Requirements for Female Participants.**

| Category                                                                           | Guidance                                                                                                                                                                                                                                                                                                                                                                                                                                                                                                                                                                                                                                                                                                                                                                                                                                    |
|------------------------------------------------------------------------------------|---------------------------------------------------------------------------------------------------------------------------------------------------------------------------------------------------------------------------------------------------------------------------------------------------------------------------------------------------------------------------------------------------------------------------------------------------------------------------------------------------------------------------------------------------------------------------------------------------------------------------------------------------------------------------------------------------------------------------------------------------------------------------------------------------------------------------------------------|
| Women who remain abstinent as their preferred usual lifestyle                      | Remain abstinent                                                                                                                                                                                                                                                                                                                                                                                                                                                                                                                                                                                                                                                                                                                                                                                                                            |
| Women in exclusively same-sex relationships as their preferred and usual lifestyle | Are not required to use contraception                                                                                                                                                                                                                                                                                                                                                                                                                                                                                                                                                                                                                                                                                                                                                                                                       |
| Women of non-childbearing potential                                                | Are not required to use contraception                                                                                                                                                                                                                                                                                                                                                                                                                                                                                                                                                                                                                                                                                                                                                                                                       |
| Women of childbearing potential (nonpregnant)                                      | 
MUST test negative for pregnancy before initiation of treatment as indicated by a negative serum pregnancy test at the screening visit, followed by repeated urine pregnancy tests during the study clinical visits.
 
AND
 
Use one NON-ORAL form of highly effective contraception listed in Table A3.
 
If a female participant is using ORAL contraceptives. They MUST switch to a non-oral method (e.g., vaginal ring or hormonal patch) OR use a barrier methoda for four weeks after starting tirzepatide for four weeks after each dose escalationb. Tirzepatide may reduce the effectiveness of oral hormonal contraceptives due to delayed gastric emptying, which is most pronounced after the first dose and diminishes over time.
 |

aOnly apply to female participants in the intervention group. Females in the control group with childbearing potential, who are using highly effective oral contraceptives, will continue their use without the need to switch for non-oral or additional barrier contraceptives.

bThe study includes a 4-week titration phase followed by 12 weeks at target doses, participants must use a non-oral highly effective method of contraception or add a barrier method for eight weeks (four weeks after IMP initiation plus four weeks after target dose escalation). After this period, participants may either return to their previous oral contraceptives (if they switched) or discontinue using a barrier method they were using concurrently.

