Tirzepatide (Mounjaro®) is a synthetic peptide that may lead to antibody formation, similar to other subcutaneously injected peptides. Participants treated with tirzepatide can develop antibodies and immune-related and hypersensitivity reactions, but their incidence is in general low and mostly mild to moderate in severity (90). If suspected, the study team will assess and refer the participant for appropriate care, and the medication will be discontinued. The study physician will contact the participant's physician.

Injection site reactions, such as rash, erythema, or itching, are common with GLP-1RAs and GIP/GLP1RAs. These reactions are most often transient and generally do not cause treatment discontinuation (91).

The possible association between tirzepatide (Mounjaro®) and the risk of pancreatitis has also been described. This association must be considered, especially in participants with several risk factors for pancreatitis, such as severe hypertriglyceridemia or alcohol intake (89,92). These participants will be excluded from the study (**See Section 7.1**). Other adverse effects of these drugs include headache and nasopharyngitis, but these effects do not usually lead to discontinuation of the drug. This medication has a rare risk of severe hypoglycemia, cholelithiasis, and cholecystitis ( $\leq 1\%$ ) (91,92).

An increase in heart rate has also been described with a dose-response relationship in the following order: Tirzepatide 15 mg > 10 mg > 5 mg (93). Participants with uncontrolled CVD and a personal history of arrhythmias will be excluded from this study (**See Section 7.1**). An ECG will be performed periodically during the study.

Tirzepatide is contraindicated in patients with a history or family history of medullary thyroid cancer and patients with multiple endocrine neoplasia type 2 (MEN-2) (53) (**See Section 7.1**).

Animal reproduction studies suggest there may be risks to the fetus from exposure to tirzepatide during pregnancy. Additionally, tirzepatide may reduce the effectiveness of oral hormonal contraceptives due to delayed gastric emptying, which is most pronounced after the first dose and diminishes over time. Female participants of childbearing potential using oral contraceptives should switch to a non-oral method (e.g., vaginal ring or hormonal patch) or use a barrier method for four weeks after starting tirzepatide and for four weeks after each dose escalation (**See annex 7** for study contraceptives guidelines).

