### 8.3 Dose modifications

In this study, participants will start with an initiation dose of 2.5 mg weekly, and after four weeks, they will receive a stable dose of 5 mg weekly. In case of intolerance to the medication, the dose can be scaled back. However, the tirzepatide dose escalation scheme has been designed to minimize the development of GI symptoms. During the dose escalation period, every effort should be made by the investigator to escalate and maintain participants on the corresponding tirzepatide dosage (maximally 5mg/week). After the stabilization, the dose modification for tirzepatide is not permitted. **See Annex 8** for the plan to mitigate gastrointestinal symptoms.

If a dose is missed, the participant will be instructed to administer tirzepatide as soon as possible, within four days (96 hours) after the missed dose. If more than four days have passed, the missed dose should be skipped, and the next dose should be administered on the regularly scheduled day. The day of weekly administration can be changed (if necessary) if the time between the two doses is at least three days (72 hours).

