#### Intervention arm:

The study staff will contact the participant to give instructions for escalation to the target dose (5 mg SC weekly). The investigators judge that participants might need more time in the titration phase. This visit can also be used to adjust the insulin pump's parameters if needed (**See Annex 3**).

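### The eight-week figure in Annex 7, Table A4 footnote b matches the protocol's event-based contraception wording only if escalation happens by week 4, and the protocol foresees later escalation

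*Protocol*

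**What the plan says.** Section 3.7 (side-effects of tirzepatide) tells women of childbearing potential on oral contraceptives to switch to a non-oral method or to "use a barrier method for four weeks after starting tirzepatide and for four weeks after each dose escalation". The body of Table A4 in Annex 7 ties the period to the same two kinds of event, the start of the drug and each escalation. Footnote a limits the measure to the intervention group.

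Footnote b converts this into a total. Its premise is the planned schedule: "The study includes a 4-week titration phase followed by 12 weeks at target doses". It then states that "participants must use a non-oral highly effective method of contraception or add a barrier method for eight weeks", and explains the total in a parenthesis: "four weeks after IMP initiation plus four weeks after target dose escalation". The release clause follows: "After this period, participants may either return to their previous oral contraceptives (if they switched) or discontinue using a barrier method".

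Other parts of the protocol allow escalation to come later than week 4. On Phone Visit 1, Section 9.3.3 says: "The investigators judge that participants might need more time in the titration phase". It gives no upper limit. Annex 8 describes the escalation period as weeks 0 to 8. Table 1 gives Phone Visit 1, the week-4 escalation call, a window of ±3 days.

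**The concern.** The footnote contains both a fixed total and an event-based definition, and the release clause refers back to the period without saying which of the two sets its end. On the planned schedule they coincide. When titration is prolonged they do not, and a site or participant working from the number eight would stop the extra method before four weeks had passed since the actual escalation.

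The measure exists because, by the protocol's own account, tirzepatide may make oral hormonal contraceptives less effective and animal studies suggest a possible risk to the fetus. Table 1 schedules pregnancy tests at week 8 and then at week 16, so a pregnancy beginning in the disputed weeks might not show on a scheduled test until the last visit.

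**Working it through.** This is calendar arithmetic; no power or error rate is involved.

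**Inputs**
- Fixed count: eight weeks = 56 days (footnote b).
- Post-escalation period: four weeks = 28 days (Section 3.7, Table A4, and the parenthesis in footnote b).
- Planned escalation: week 4 = day 28 (premise of footnote b; Phone Visit 1 in Table 1).
- Window of Phone Visit 1: ±3 days (Table 1).
- Assumptions: the first dose is on day 0 and escalation takes place on the day shown.

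**Formulas**
- End of event-based period = escalation day + 28.
- Shortfall of a continuous count from the first dose = max(0, escalation day + 28 − 56).

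**The plan's own figure.** Escalation on day 28 gives 28 + 28 = 56 days = eight weeks. The footnote's number is reproduced.

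**Other escalation dates**

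| Escalation | Day | Event-based end | Shortfall of 56-day count |
|---|---|---|---|
| Week 4 − 3 days | 25 | day 53 | 0 |
| Week 4 | 28 | day 56 | 0 |
| Week 4 + 3 days | 31 | day 59 | 3 days |
| Week 5 (assumed) | 35 | day 63 | 7 days |
| Week 6 (assumed) | 42 | day 70 | 14 days |
| Week 8 (assumed; end of the Annex 8 escalation period) | 56 | day 84 | 28 days |

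The shortfall equals the delay beyond week 4. At week 8 the fixed count ends on the day of escalation, so none of the following four weeks is covered.

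**The alternative reading.** If the parenthesis governs, the second four weeks start at the actual escalation and the shortfall after escalation is zero for every date. The time between week 4 and a late escalation is then not addressed, but Section 3.7 and the body of Table A4 leave it open in the same way, so on that point the passages do not disagree with one another.

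**The case against.** The strongest reply is that the sentence giving eight weeks goes on to define it by dose events. On that reading the release clause refers to the period so defined, the eight is just the sum for the planned schedule, and a late escalator still has four weeks after escalation. The event-based wording of Section 3.7 and the body of Table A4 applies in any case. This stands in part: early release follows from one reading of the footnote and is not an unconditional rule. It does not remove the problem, because the sentence still states a number that is wrong for any escalation after week 4.

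It is also fair to object that weeks 6 and 8 are not planned escalation dates. They are illustrations. Only the 3-day case comes directly from a stated window.

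A reader might infer three further things that the documents do not support.

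- **Repeated escalation after scale-back.** Section 8.3 says "In case of intolerance to the medication, the dose can be scaled back", which might suggest a second escalation. Re-escalation is described nowhere, a scale-back is not itself an escalation, and Section 8.3 bars dose modification after stabilization.
- **An ineffective barrier method.** Table A3 lists "Barrier protection methods without the concomitant use of a spermicide" as ineffective, while Table A4 accepts a barrier method without qualification. In footnote b, however, the barrier is added to an oral method that Table A3 classes as highly effective, and Table A5 accepts plain condoms alongside a partner's highly effective method. This is not a clear contradiction.
- **A threat to the size of the 21-participant arm.** The protocol gives no figure for oral-contraceptive users or late escalators, so no such loss can be estimated.

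**Conclusion.** The point holds as an internal ambiguity of minor severity. Footnote b's eight weeks and its release clause agree with the event-based wording only when escalation occurs by week 4, and Section 9.3.3, Annex 8 and the Table 1 window each admit later escalation. Read as a continuous count from the first dose, the footnote falls short by the length of the delay: 3 days at the edge of the visit window, and 2 or 4 weeks if escalation is assumed at week 6 or week 8. Read through its parenthesis, it does not fall short after escalation.

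The conclusion rests on the continuous count being a plausible reading and on some participants escalating late; the protocol does not say how many. It concerns only intervention-arm women of childbearing potential who use oral contraceptives and escalate after week 4. A reader might conclude that footnote b orders the release of these women too early. The text does not go that far.

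**What to change.** Reconcile the eight-week figure and the release clause in Annex 7, Table A4 footnote b with Section 3.7, the body of Table A4, Section 9.3.3 and Annex 8, so that the footnote and the event-based wording cannot give different end dates for the same participant. Which rule applies, and for how long, is for the investigators to decide; none is proposed here.

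The cost is a wording change in Annex 7 and, where the eight weeks is repeated, in the participant materials. Dosing dates are already recorded weekly in the medication logbook (Section 8.4), so no new data collection is needed. No analysis or sample size is affected.

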## Contraception Guidance

### Contraception Requirements for Male Participants in the Intervention Arm

All men in the intervention arm should refrain from sperm donation and follow the contraception guidance in **Table A5**. for the duration of the study and until 30 days following the last dose of the IMP.

**Table A5. Contraception Requirements for Male Participants (Intervention Arm)**

| Category                                                                                                                                                                                                     | Guidance                                                                                                                                                                                                                                                                                                                                                                               |
|--------------------------------------------------------------------------------------------------------------------------------------------------------------------------------------------------------------|----------------------------------------------------------------------------------------------------------------------------------------------------------------------------------------------------------------------------------------------------------------------------------------------------------------------------------------------------------------------------------------|
| Men who remain abstinent as their preferred usual lifestyle                                                                                                                                                  | Remain abstinent                                                                                                                                                                                                                                                                                                                                                                       |
| Men in exclusively same-sex relationships, as their preferred and usual lifestyle                                                                                                                            | Are not required to use contraception                                                                                                                                                                                                                                                                                                                                                  |
| Men with partners of childbearing potential (nonpregnant)                                                                                                                                                    | 

- Use condoms and the partner an additional highly effective method of contraception listed in Table A3.

 
OR
 

- Use condoms with spermicide and the partner an additional effective method of contraception such as diaphragms with spermicide, or cervical sponges

 |
| Men with partners of non-childbearing potential (postmenopausal females or females with tubal ligation hysterectomy or bilateral oophorectomy or have a congenital anomaly, for example, Mullerian agenesis) | Are not required to use contraception                                                                                                                                                                                                                                                                                                                                                  |
| Men who had a vasectomy or testicular removal surgery or who are sterile due to other medical conditions                                                                                                     | Are not required to use contraception                                                                                                                                                                                                                                                                                                                                                  |
| Men with pregnant partners                                                                                                                                                                                   | Use condoms                                                                                                                                                                                                                                                                                                                                                                            |

